**Laboratory investigational plan**

- Parasite Evaluation by Microscopy of lesion tissue: At Day 0 and EOT in both the groups and then every follow up visit till 12 months.
- Biochemical Evaluation: serum bilirubin, SGPT, SGOT, BUN, serum creatinine, sodium and potassium during Study period (Day 0, Day 15 , Day 30) of every course of treatment and then every follow up visit till 12 months in both the groups.
- Haematological Evaluation: Routine Haematological investigations like TC/DC (WBC), haemoglobin, platelet count during Study period (Day 0, Day 15, Day 30) of every course of treatment and then every follow up visit till 12 months in both the groups.
- Parasite load: By qPCR at day 0 and at the end of the treatment at lesion tissue .

**Withdrawal during study**: Any PKDL patient who develops the following will be withdrawn from the study:

- ASAT, ALAT, AP >3 times upper limit of normal range
- Bilirubin >2 times upper limit of normal range
- Serum creatinine or BUN >1.5 times upper limit of normal range
- Any serious adverse event
- Subject’s withdrawal if there willingness to discontinue from participation in study

**Expected Outcome:** Assessment of Amphotericin B (0.5 mg/kg body wt) low dose as a safe and effective for treatment of all types PKDL

**Duration of the study**: Three years

**Estimated Budget:** 10 Lakhs

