**PROJECT TITLE:** To evaluate efficacy and **s**afety of Amphotericin B in two different doses in the treatment of Post Kala-Azar Dermal Leishmaniasis (PKDL)

PI- Dr [name]

Co-Investigator- [name], [name], [name], [name], & [name].

- ***Primary Objective:***
- To evaluate the efficacy and safety of Amphotericin B in different doses in the treatment of PKDL
- **Secondary Objectives:**
- To assess the efficacy of two doses in the treatment of PKDL.
- To evaluate parasite load in the skin lesion by qPCR.
- To evaluate the safety of drug with the help of clinical, haematological and biochemical parameters during the course of treatment.

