**Study Design**

The study is a randomized, open label study, designed to establish that Amphotericin B therapy can be drug of choice for the treatment of PKDL cases. In this study to assess safety and efficacy of Amphotericin B for the treatment of Post Kala-azar Dermal Leishmaniasis in two different doses modalities.

**Patients’ eligibility:** The patients will be selected from the out-patient department of Rajendra Memorial Research Institute of Medical Sciences (ICMR), Patna, India. They will be admitted in the ward and treated according to the group given (A and B).

*Inclusion criteria:*

- Both sex patients aged 5-60 years
- Parasitologically confirmed Post kala azar dermal leishmaniasis (PKDL),
- All types of PKDL.

*Exclusion criteria:*

- Pregnant and lactating females.
- Patients not willing to participate.
- Individuals who were sero positive for HIV
- Individuals with a serious concurrent infection (e.g., tuberculosis or bacterial pneumonia) were excluded from the study.
- Thrombocyte count <100 x 10^9^/l
- Leukocyte count <2.5 x 10^9^/l
- Hemoglobin < 6.0 g/100 ml
- ASAT, ALAT, AP >3 times upper limit of normal range
- Bilirubin >2 times upper limit of normal range
- HbsAg, HCV and HIV positive
- Serum creatinine or BUN >1.5 times upper limit of normal range
- Relapsed PKDL cases

**Sample Size**: 50 in numbers after reviewing inclusion and exclusion criteria, eligible patients will be enrolled in two different groups (25 in each group).

**Test Arm: “**Group A” will receive Amphotericin B in the dose of 0.5 mg/ Kg body weight daily for 20 infusions at 15 days interval followed 3 courses.

**Control Arm***:* “Group B” will receive Amphotericin B in the dose of 1mg/kg body weight for 20 infusions in 5% dextrose on alternate days in 3 courses at 15 days interval.

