**Randomization:**

All the patients will be administered an informed consent before starting any trial related activities. Open label un-blind randomization will be done through sequentially numbered sealed envelopes prepared from a computer-generated randomization sequence.

All routine investigations like TC/DC(WBC), haemoglobin, platelet count and biochemical investigations like serum bilirubin, SGPT, SGOT, BUN, serum creatinine, sodium and potassium will be done on 0, 15 , 30 days.

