**Study assessments:**

***Safety:*** Safety will be assessed by collection of the following:

- All serious adverse events (SAEs) from time of admission through 12-month follow-up visit after end of treatment (EOT)
- All adverse events from time of first dose through EOT
- Clinical vital signs daily

***Efficacy:*** Efficacy will be assessed by collection of the following:

- **Parasitological cure**: defined as clearance of parasite from the dermal lesions that is Grade 0 parasite score in the dermal lesion at the end of treatment.
- **Final Clinical cure**: Define as total disappearance of skin lesion and Grade 0 parasite score at twelve months follow up.

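### Laboratory checks on Day 0, 15 and 30 of each course miss the end of dosing in both arms, and Day 30 is off drug in Group A but on drug in Group B (minor)

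*Protocol*

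**What the plan says.** Study Design gives both arms 20 infusions per course in 3 courses. Group A receives 0.5 mg/kg "daily for 20 infusions at 15 days interval followed 3 courses"; Group B receives 1 mg/kg "for 20 infusions in 5% dextrose on alternate days in 3 courses at 15 days interval".

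The Laboratory investigational plan sets one calendar for both arms. Biochemistry is scheduled at "Day 0, Day 15 , Day 30) of every course of treatment and then every follow up visit till 12 months in both the groups", and haematology follows the same days. The Randomization section gives the same days, "will be done on 0, 15 , 30 days", without saying that they apply to each course. No blood test is tied to an infusion number or to the end of a course. Microscopy and qPCR of lesion tissue are planned at end of treatment; haematology and biochemistry are not.

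Two uses depend on these samples. One secondary objective is "To evaluate the safety of drug with the help of clinical, haematological and biochemical parameters during the course of treatment". Under Withdrawal during study, the limits for transaminases, alkaline phosphatase, bilirubin, creatinine and BUN remove a patient from the study. Other safety data are serious adverse events, "All adverse events from time of first dose through EOT" and "Clinical vital signs daily".

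**The concern.** A common calendar suits arms whose courses last equally long. Here one course takes almost twice as long as the other, so the same day number can mean active dosing in one arm and rest in the other. A table of Day 30 values by arm would then set recovery against exposure.

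The second issue applies to both arms. The sample most informative about a course is the one taken when the full course dose has been given, and neither arm has it. What is at stake is patient protection, because the withdrawal limits act only on values that are measured, and a laboratory safety comparison that can be interpreted. Analysis cannot recover samples that were never drawn, so this is a matter for the protocol's schedule and not for an analysis plan.

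**Working it through.** **Inputs.** From Study Design: 20 infusions per course, 3 courses, 15-day interval, A daily at 0.5 mg/kg, B on alternate days at 1 mg/kg. From the Laboratory investigational plan: checks on Day 0, 15 and 30 of each course.

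**Reading used.** The 15 days are taken as the gap between courses. They cannot run from start to start, since 20 daily infusions already take 20 days. The protocol does not say whether the first infusion is on Day 0 or Day 1, so both are shown. Blood is assumed to be drawn before that day's infusion.

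**Course length** = 1 + step × (20 − 1): A 1 + 1 × 19 = 20 days; B 1 + 2 × 19 = 39 days.

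| | Group A | Group B |
|---|---|---|
| Infusion days, first on Day 0 | 0 to 19 | 0, 2, …, 38 |
| Infusion days, first on Day 1 | 1 to 20 | 1, 3, …, 39 |
| Given before Day 15 | 15 or 14 (7.5 or 7 mg/kg) | 8 or 7 (8 or 7 mg/kg) |
| Given before Day 30 | 20 (10 of 10 mg/kg) | 15 (15 of 20 mg/kg) |
| Day 30 against last infusion | 30 − 19 = 11 or 30 − 20 = 10 days after | 38 − 30 = 8 or 39 − 30 = 9 days before |
| Infusions left after last on-dosing check | 20 − 15 = 5 or 20 − 14 = 6 | 20 − 15 = 5 |
| First check after last infusion | Day 30, 10-11 days later | Day 0 of next course, about 15 days later; after course 3, an undated follow-up visit |

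**Day 15** is a fair comparison point: 7-7.5 mg/kg given in A and 7-8 mg/kg in B, both arms on drug. **Day 30** is not: A has finished the course and is resting, while B had an infusion 1-2 days earlier and has 5 to come.

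**Number of checks.** Each arm has 3 × 3 = 9 scheduled checks, of which 9 − 1 = 8 follow the first dose of the trial. Checks during dosing, with Day 0 taken as a pre-dose sample: A 1 × 3 = 3, B 2 × 3 = 6. Per day of dosing: A 3/(3 × 20) = 3/60 = 0.050; B 6/(3 × 39) = 6/117 = 0.051.

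**The case against.** A reader might infer from the 3 and 6 on-dosing checks that the schedule is biased towards Group A, the arm the protocol expects to show as safe. The documents do not support that, for four reasons.

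- All 8 checks after the first dose can trigger withdrawal, including A's Day 30 and Day 0 of courses 2 and 3. The limits are not confined to on-dosing samples.
- Twice the checks goes with about twice the time on drug, and the density per dosing day is nearly equal. B also receives 60 mg/kg in total against 30, so more events seen in B could be real.
- The direction is not one-way. A is checked 10-11 days after its last infusion and B only after about 15, so an end-of-course rise that resolves in between can be seen in A and missed in B.
- A numerical bias needs assumptions from outside the document. With an assumed 5% chance of crossing a limit at each on-dosing check, independent checks and full recovery by A's Day 30, one gets 1 − 0.95³ = 14.3% in A against 1 − 0.95⁶ = 26.5% in B. The gap is zero if rises persist to Day 30, or if checks within a patient are perfectly correlated.

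Two further inferences also go too far. That Group B would lose more patients from the 12-month cure outcome depends on how withdrawn patients are followed and handled, which this document does not settle. That A's last Day 30 check lies outside the adverse-event window depends on a definition of end of treatment that is not given.

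It can also be said that adverse events, serious adverse events, daily vital signs and ward admission protect patients. They do, but they do not measure creatinine or liver enzymes. All these objections stand against a claim of bias. None of them supplies the missing end-of-dosing sample or makes Day 30 comparable.

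**Conclusion.** The point holds as a minor one. The common schedule puts Day 30 10-11 days off drug in Group A and on drug in Group B. It leaves the last 5-6 infusions of each course in A and the last 5 in B without a timely laboratory check. Rises in creatinine, BUN, liver enzymes or bilirubin that peak at the end of a course and then recover can go unseen in either arm. A lasting rise would still be found at the next scheduled check.

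This rests on reading the 15 days as the gap between courses, on blood being drawn before the day's infusion, and on the schedule applying to every course, as the Laboratory investigational plan says. Starting on Day 0 or Day 1 changes the figures only within the ranges shown. No size or net direction of bias between the arms is claimed.

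**What to change.** In the Randomization section and the Laboratory investigational plan, replace the Day 0, 15 and 30 wording by: *Haematology and biochemistry are done in both groups on Day 0 and Day 15 of every course and within 24 hours after infusion 20 of every course, in Group B also on Day 30 of every course, and then at every follow-up visit until 12 months.* Compare the arms' laboratory values at Day 0, Day 15 and end of dosing, and use Day 30 in Group B as an on-dosing safety check only.

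Cost: Group A has no extra samples, because the end-of-dosing sample replaces Day 30. Group B has 1 × 3 = 3 more per patient, or 3 × 25 = 75 in total, taken around an infusion already being given. No new clinical limit is needed.

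Downside: Group A loses its rest-period check. Day 0 of the next course falls only about 4-6 days after Day 30, and after course 3 recovery is seen at the follow-up visits.

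Re-timing every check by infusion number (before infusions 1, 8 and 15 and after 20) is not recommended. It gives 9 checks after dosing starts in each arm, or 9/60 = 0.150 per dosing day in A against 9/117 = 0.077 in B, and so replaces one imbalance with another.

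### Patients who reach a laboratory limit or have an SAE leave the study, not only the drug, so their later safety and 12-month cure data are not collected

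*Protocol*

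**What the plan says.** In the protocol, section Laboratory investigational plan, the paragraph headed "Withdrawal during study" opens with the rule that "Any PKDL patient who develops the following will be withdrawn from the study". Five items follow under that one lead-in:

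- for liver enzymes, the trigger is "ASAT, ALAT, AP >3 times upper limit of normal range"
- for bilirubin, a value more than twice the upper normal limit
- for kidney function, the trigger is "Serum creatinine or BUN >1.5 times upper limit of normal range"
- for clinical events, "Any serious adverse event", with no condition on cause or timing
- last, the patient's "willingness to discontinue from participation in study"

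Other parts of the protocol set these data requirements:

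- **Study assessments, Safety:** all SAEs are collected from admission to the visit 12 months after EOT.
- **Study assessments, Efficacy:** final clinical cure needs both lesion disappearance and a Grade 0 parasite score at twelve months.
- **Laboratory investigational plan:** microscopy is done "At Day 0 and EOT in both the groups and then every follow up visit till 12 months". The biochemical and haematological tests likewise continue at each follow-up visit to 12 months.

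Efficacy and safety together are the primary objective. The sample size is 50, with 25 per group.

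**The concern.** The rule is mandatory, and what the patient leaves is the study. Reaching a creatinine limit has the same consequence as refusing further participation. If site staff follow the text, a patient's data end at the first laboratory breach or SAE. It then remains unknown whether the abnormality resolved, whether further SAEs occurred, and whether the lesions had cleared at 12 months.

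The triggers are themselves safety outcomes, in a trial that compares 0.5 mg/kg daily with 1 mg/kg on alternate days. The missing data would therefore be related to safety and could differ between the groups. An SAP can say how a withdrawn patient is counted. It cannot supply observations that the protocol told staff not to make.

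**Working it through.** The protocol states no figure on this point, so there is none to reproduce. The check has two parts.

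**1. Reading the rule against the data requirements**

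| Data required | Where | For a patient who meets a laboratory or SAE criterion |
|---|---|---|
| All SAEs to 12 months after EOT | Study assessments, Safety | Ends at the first triggering event |
| Final cure at 12 months | Study assessments, Efficacy | Not observed |
| Microscopy to 12 months | Laboratory investigational plan | Ends |
| Liver and renal tests to 12 months | Laboratory investigational plan | Ends, so recovery is not documented |

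No section provides for continued observation of withdrawn patients.

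Timing matters as well. The rule covers the whole study, and SAEs and laboratory values are collected to 12 months after EOT. An SAE of any cause at, say, month 8 of follow-up would trigger withdrawal although dosing is over. At that point the rule can only end observation.

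**2. Scale of the loss**

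Inputs: 25 patients per group (Study Design, Sample Size). The numbers lost are assumptions, because the protocol gives no withdrawal rate.

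Let cA and cB be the numbers cured among those who stay, and kA and kB the numbers lost.

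- Cure in A lies between cA/25 and (cA + kA)/25; B likewise.
- The difference A − B lies between (cA − cB − kB)/25 and (cA + kA − cB)/25.
- The width of that range is (kA + kB)/25, which does not depend on cA or cB.

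| Total lost, both groups (assumed) | Width of range |
|---|---|
| 1 | 1/25 = 4 points |
| 3 | 3/25 = 12 points |
| 5 (10% of 50) | 5/25 = 20 points |

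An unequal loss shows how the handling of missing outcomes can change the answer. Assume 1 lost in A and 5 in B, with about 90% cured among those who stay: 22 of 24 in A and 18 of 20 in B.

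- Patients who stay: 22/24 − 18/20 = 0.917 − 0.900 = about +2 points.
- Lost patients counted as failures: 22/25 − 18/25 = +16 points.
- Extremes: (22 − 18 − 5)/25 = −4 points to (22 + 1 − 18)/25 = +20 points. The width is 24 points = 6/25, as the formula gives.

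The choice of which group loses more is arbitrary and is not a prediction.

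**The case against.** The strongest reply is that the sponsor meant only that treatment stops. The protocol never says in words that follow-up ends. The three laboratory limits are the same as those in the exclusion criteria, which suggests a test of fitness to receive amphotericin B. The SAE window exempts no withdrawn patient, so SAE collection could be taken to continue. A visit schedule may also be read as applying only to patients still in the study, in which case it does not contradict a rule about who leaves.

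Part of this stands. That follow-up ends is an inference from the wording and from the lack of any provision for it. But matching limits do not turn leaving the study into stopping the drug, and consent withdrawal sits in the same list with the same consequence. The SAE window creates the tension and does not resolve it. The stop-drug reading also cannot explain what the rule does after EOT.

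Four smaller points are fair and leave the core intact:

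- The SAE criterion has no causality condition, so not every patient lost would have drug toxicity.
- Alkaline phosphatase is a trigger but is not in the scheduled biochemical panel, so planned tests would not detect that breach.
- Counting withdrawn patients as failures, if an SAP does so, would give a defined cure analysis. It would not reveal their true lesion status, later SAEs or recovery.
- The 4-point step applies to any missing outcome with 25 per group, whatever its cause.

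**Conclusion.** The concern holds. As worded, the rule removes patients from observation because of safety events, while the same protocol asks for safety and cure data on patients up to 12 months. This is a conduct rule that the protocol fixes badly, and not a detail that can wait for the SAP.

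Its actual size is unknown, because the documents fix neither the number of such withdrawals nor their split between groups. The 4, 12 and 20 points are worst-case ranges for assumed losses of 1, 3 and 5 patients. They are not estimates of bias, and no direction is claimed. The conclusion rests on the plain reading of the rule. If the sponsor intended treatment discontinuation only, the text still needs correcting, because sites have no way to know that. It should be fixed; confidence is medium because that intent cannot be seen from the document.

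**What to change.** In the withdrawal paragraph of Laboratory investigational plan:

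- For the laboratory limits and SAEs, replace withdrawal from the study with *discontinued from study drug*.
- Add: *These patients remain in scheduled follow-up (SAEs, laboratory tests, lesion assessment, microscopy) to 12 months unless they withdraw consent. Any other antileishmanial treatment is recorded. After EOT, such events are recorded and do not end participation.*
- List the patient's own withdrawal separately, as the only route out of the study.

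The cost is a change of wording, continued attendance of the affected patients at visits already planned, and one added data item (other antileishmanial treatment). No new procedure is needed. The drug is still stopped at the same limits, so patient protection is not reduced, and patients with toxicity gain monitoring.
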